**Fig. 2 Fig2:**
[figure not shown]
Estimated monthly referral flow

The numbers of potential participants at each stage of the selection process during each month of the feasibility study is shown in Fig. 2. Based on audit and best information across our trial sites, we estimate that each month, parents of 200 newly referred children (of roughly 750 referrals across the 5 sites) will be eligible to take part in the feasibility study. We estimate that 50 parents would consent to the feasibility study and of these roughly 25 will give a positive response to the feasibility question, which is above the number required.

We will test this by recruiting 25 study eligible parents (half of the number available) each month (100 over 4 months). Our projections will be supported if 12 or so of these parents answer the feasibility question positively. This number will also give us a good sample in which to assess our other feasibility measures.

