## Methods

### Study objective

The primary objective of the study is to test whether we can use our remote recruitment, consenting and assessment strategy to recruit recent referrals to children’s services (CAMHS and early behavioural support services) at a sufficient monthly rate to provide statistical power for our planned STEPS RCT.

Secondary objectives include establishing the usability and acceptability of our remote recruitment, consenting and assessment strategy including the online outcome and adverse events collection procedure. We will also assess the feasibility of collecting teacher data remotely within the required timeframe and capture technical difficulties completing online questionnaires.

This study will not pilot or test the feasibility of the STEPS app as a form of a parent training intervention.

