### Outcomes

The primary outcome for this study is the number of eligible feasibility study participants who *agree in principle* to take part in a full RCT of STEPS each month.

Agreement in principle to take part in the upcoming STEPS RCT: feasibility study participants will each be given a balanced explanation of what an RCT involves (see 2. Feasibility Question Script in Supplementary Documents) and asked. “*if there was an RCT of STEPS would they be willing to take part in it*?” After being asked the question parents will be given a choice of a YES/NO answer. Parents, who answer ‘NO’, will be asked to provide a brief explanation for their decision. The researcher will note a parent’s answer and any comments on the data form.

Secondary feasibility outcomes concerning the secondary study objectives are shown in Table 1.

**Table 1 Tab1:** Secondary feasibility outcomes

To pilot the remote consenting procedure, an online outcome and adverse events collection procedure.	To assess the feasibility of collecting teacher data remotely within the required timeframe.	To capture technical difficulties with completing online questionnaires.
*Remote consenting procedure:* • Mean time taken to complete remote consenting procedures. • Parents’ mean ratings of satisfaction with consenting procedures. • Content analysis of text box evaluations.	• Mean time to identify teachers. • The proportion of teachers’ questionnaires returned within 7 days of receiving a link to an online survey out of the number of teachers recruited	• Qualitative description of technical difficulties with accessing or completing online questionnaires.
*Online outcome collection:* • The proportion of participants completing outcome questionnaires within 7 days of receiving a link to an online survey out of the number of participants who are in the study. • Mean number of reminder emails about completing outcome questionnaires sent to parents by the research team. • Parents’ mean ratings of satisfaction with online data collection. • Content analysis of free text evaluations.		
*Online adverse events collection:* • The proportion of participants completing the adverse events questionnaire within 7 days of receiving a link to an online survey out of the number of participants who are in the study. • Mean number of reminder emails about completing adverse events questionnaire sent to parents by the research team.		

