### Sample size

The primary aim of the feasibility study is to establish that we can recruit enough parents of new referrals for the STEPS RCT using our remote strategy incorporating existing routine CAMHS triage and clinical screening elements using MHE, ICAN or telephone-based methods across the five recruitment sites (Fig. 2). Based on the power calculations for the larger planned RCT of STEPS, we need to recruit 13 participants a month (352 families over 27 months). We will base our assessment of whether this is possible on the primary feasibility outcome described above, the rate per month of participants who answer the STEPS RCT feasibility question in the affirmative. Because we assume it is more likely that people would agree in principle to take part in STEPS RCT during the feasibility study than would actually consent to the real trial, we have adopted a conservative requirement in this feasibility of 18 (rather than 13) parents a month as our aim in this feasibility study and our stop/go criterion for the larger trial.

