#### Method 1: myHealthE portal

In some of the participating organisations, CAHMS triage and rapid screening for hyperactivity/impulsivity, inattention and challenging behaviour occur as part of routine care using myHealthE (MHE; https://www.slam.nhs.uk/our-services/camhs/get-involved/myhealthe/)—a Caldicott Guardian approved, General Data Protection Regulation (GDPR) compliant, online portal for the automated screening of referred families using NHS CAMHS data [18, 33]. MHE uses a secure text/email system through which primary caregivers are invited to register and complete validated clinical screening measures using an online portal. These are then automatically coded using standard algorithms to subsequently allow the research team to identify potentially eligible parents. MHE also seeks parents’ permission to be contacted with invitations to take part in research studies; that is, provide consent-for-contact. By consenting to research contact, parents also give their permission for Trust-approved researchers to review their children’s medical records to establish eligibility.

Authorised staff at each participating clinic site will regularly input the new referrals’ details into MHE, which will initiate the mechanism for obtaining the initial consent for research contact and for obtaining the screening information. Members of the research team will regularly log into the MHE researcher portal (this portal only includes information about children’s whose parents gave consent for contact) to check for any new cases flagged up as ‘eligible’. At each organisation, a member of the research team will identify potential participants by reviewing cases flagged up as ‘eligible’ by MHE using a standard algorithm. To be flagged as ‘eligible’ the case has to fulfil the following criteria: (1) a child is aged 5 years 0 months to 11 years 11 months, (2) a child screened positive for ADHD-type problems and challenging behaviour on the SDQ; (3) a child is not under local authority care; and (4) a parent provided routine consent for research contact. The ‘eligible’ flag will be treated as a potential participating family.

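### Enrolling 25 parents a month cannot confirm the assumed flow of 50, and the 12-of-25 threshold is not reconciled with the stop/go criterion of 18 a month

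*Protocol article*

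**What the plan says.** All references are to the protocol article.

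- Study objective: the aim is to learn whether the remote strategy recruits "at a sufficient monthly rate to provide statistical power for our planned STEPS RCT".
- Outcomes: the primary outcome is a monthly count, "the number of eligible feasibility study participants who" say they would join the full RCT.
- Sample size, RCT requirement: "we need to recruit 13 participants a month (352 families over 27 months").
- Sample size, decision measure: "the rate per month of participants who answer the STEPS RCT feasibility question in the affirmative". The threshold is "18 (rather than 13) parents a month as our aim in this feasibility study and our stop/go criterion for the larger trial". The Statistical analysis section repeats the aim of 18 a month and mentions no scaling.
- Sample size, text after Fig. 2: from site audit and best estimates, about 200 of roughly 750 monthly referrals would be eligible, 50 parents would consent and about 25 would answer yes. The test of this is stated as "We will test this by recruiting 25 study eligible parents (half of the number available) each month (100 over 4 months"). About 12 positive answers among the 25 would support the projections. The abstract gives 100 as the maximum sample.

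**The concern.** The study exists to measure a monthly flow. Enrolling 25 a month estimates the proportion answering yes and shows that at least 25 parents could be found. It does not show whether another 25 were available. A network that can supply 25 consenters a month and one that can supply 50 give the same primary data once 25 are enrolled.

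The threshold of about 12 makes sense only if the second 25 exist. The article states no conversion between 12 of 25 and 18 a month, so the steering committee that decides on progression (Data monitoring section) could read the same result as support or as failure. What is at stake is the primary outcome and the only numerical stop/go criterion in the article.

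**Working it through.** **Inputs** (all from Sample size): RCT need 352 families in 27 months; stop/go 18 a month; projected 50 consenters and 25 positive answers a month; planned enrolment 25 a month for 4 months; support threshold about 12.

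**1. The plan's own figures reproduce.**
- 352 / 27 = 13.04, stated as 13.
- 25 × 4 = 100.
- Projected positive share: 25 / 50 = 50%.
- Expected positives among 25: 25 × 0.50 = 12.5, stated as about 12.
- Scaled up: 12 × (50/25) = 24, which exceeds 18. Unscaled, 12 is below both 18 and 13.

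The figures therefore fit together only with the factor 50/25 = 2.

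**2. Treat the flow as unknown.** Let F be the number of consenters available per month. A result of 12 of 25 (48%) projects to 0.48 × F.

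| F (consenters a month) | Projected positives a month | Meets 18? |
|---|---|---|
| 25 | 12.0 | no |
| 30 | 14.4 | no |
| 35 | 16.8 | no |
| 37.5 | 18.0 | yes, just |
| 40 | 19.2 | yes |
| 50 | 24.0 | yes |

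Break-even: 18 / 0.48 = 37.5 consenters a month. At exactly 50% positive it is 18 / 0.50 = 36.

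The support threshold does not respond to F once F is at least 25. With a true positive share of 50%, the chance of 12 or more among 25 is 0.65 in one month, and of 48 or more among 100 it is 0.69, whether F is 25 or 50.

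**3. Read the criterion without scaling.** The required share is 18 / 25 = 72%, against the projected 50%. Exact binomial probabilities at 50%:
- P(18 or more of 25) = 0.022 in one month.
- P(72 or more of 100) = 0.000006 over four months (72 = 18 × 4).

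**4. Three possible thresholds.** Unscaled, the criterion is 18 of 25. Scaled by the assumed factor it is 18 × (25/50) = 9 of 25. The stated support threshold of about 12 is neither of these: it is the projection of 25 halved.

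**The case against.** Several points on the other side are sound.

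- **Scaling is not a stated analysis step, and support for the projections is not the same as a decision to proceed.** A reader might infer that the plan would launch an under-recruiting RCT on 12 positive answers a month. The documents do not support that as a stated outcome: read literally, 12 fails the criterion of 18. A false go follows only if the committee applies the implied doubling.
- **Flow is partly tested.** Enrolling fewer than 25 a month would refute the 50. The gap is one-sided, and above 37.5 consenters a month (at 48% positive) the conclusion would be right.
- **An article condenses the full protocol, and the analysis plan is described as still being developed.** Screening logs may exist there. The Discussion also says that the identification methods will be compared, which would be hard without counts by method. So the absence of a log is not the point. The point is that the published threshold uses no such count.
- **The portal.** A reader might object that under Method 1 researchers see only children "whose parents gave consent for contact", so the 200 eligible families are hidden. This adds little. Families without that consent cannot be approached by that route, so the contactable pool is what governs recruitment, and researchers can see it.
- **RCT shortfall.** One might compute 12 × 13/18 = 8.7 recruits a month, hence 234 of 352 families in 27 months, or about 41 months to finish. That treats 13/18 as an estimated conversion rate and takes the worst flow that still fills the target. The article presents 18 as a cautious margin, not a measured conversion, so these figures should not be relied on.

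What remains is that reaching 25 does not establish 50, and that 12 of 25 and 18 a month have no stated relation.

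**Conclusion.** The concern holds in this form. The support threshold and the stop/go criterion are on different scales, and the only factor that reconciles them is the assumed flow that the study is meant to test.

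- On the scaled reading, for a true flow of 25 to just under 37.5 consenters a month, the projections would be called supported while the real rate was 12 to under 18.
- On the unscaled reading, the criterion would almost surely fail even if the projections were correct.

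The size rests on a positive share of 48% (12 of 25), on the article's own 25, 50 and 18, and, for the unscaled probabilities, on independent answers at the projected 50%. Fig. 2 is not shown, but the text beside it gives the figures used here.

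**What to change.** State the stop/go criterion and the 12-of-25 threshold on one scale. By site and month, record:

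1. new eligible families with consent for contact;
2. families approached, taken consecutively;
3. families consenting;
4. families answering yes.

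Define the projected rate as (1, per month) × (consent proportion among those approached) × (yes proportion among consenters), and compare it with 18. Do not scale up the observed count unless these counts show contactable families who were not used. Counting new families each month matters because the inclusion criteria admit children who have waited up to six months, so early enrolment can draw on families already waiting.

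The first term must be the contactable families, not all eligible ones. With assumed figures of 200 eligible, 100 contactable, 50% consenting and 50% answering yes, the achievable rate is 100 × 0.5 × 0.5 = 25 a month, whereas starting from all eligible families would give 50. Eligible families without consent for contact may also be uncountable under ICAN, where the SDQ is requested from parents who have given that consent.

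The cost is a small amount of logging. Since the Study status section says recruitment is complete, it may instead be retrieval of aggregate counts from the five sites, plus revised wording in the Sample size and Statistical analysis sections. No extra participants are needed. The downside is that the projected rate may prove less favourable.

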### Recruitment

As part of our remote strategy, participants will be identified using one of three methods—depending on the current practice of the Trust from which they are being recruited:

#### Method 1: myHealthE portal

In some of the participating organisations, CAHMS triage and rapid screening for hyperactivity/impulsivity, inattention and challenging behaviour occur as part of routine care using myHealthE (MHE; https://www.slam.nhs.uk/our-services/camhs/get-involved/myhealthe/)—a Caldicott Guardian approved, General Data Protection Regulation (GDPR) compliant, online portal for the automated screening of referred families using NHS CAMHS data [18, 33]. MHE uses a secure text/email system through which primary caregivers are invited to register and complete validated clinical screening measures using an online portal. These are then automatically coded using standard algorithms to subsequently allow the research team to identify potentially eligible parents. MHE also seeks parents’ permission to be contacted with invitations to take part in research studies; that is, provide consent-for-contact. By consenting to research contact, parents also give their permission for Trust-approved researchers to review their children’s medical records to establish eligibility.

Authorised staff at each participating clinic site will regularly input the new referrals’ details into MHE, which will initiate the mechanism for obtaining the initial consent for research contact and for obtaining the screening information. Members of the research team will regularly log into the MHE researcher portal (this portal only includes information about children’s whose parents gave consent for contact) to check for any new cases flagged up as ‘eligible’. At each organisation, a member of the research team will identify potential participants by reviewing cases flagged up as ‘eligible’ by MHE using a standard algorithm. To be flagged as ‘eligible’ the case has to fulfil the following criteria: (1) a child is aged 5 years 0 months to 11 years 11 months, (2) a child screened positive for ADHD-type problems and challenging behaviour on the SDQ; (3) a child is not under local authority care; and (4) a parent provided routine consent for research contact. The ‘eligible’ flag will be treated as a potential participating family.

#### Method 2: Interactive CAMHS Assessment Network (ICAN)

In NELFT, routine outcome measures are collected through the Interactive CAMHS Assessment Network (ICAN). It is a digital application in which clinicians, young people, parents, carers and teachers can provide routine clinical measures. ICAN provides useful feedback to clinicians to help track progress and data in real-time and is directly linked to the electronic patient record.

Parents of patients, who provide consent for research contact through ICAN, will be asked to complete the SDQ also through ICAN. This information will be then passed onto the research team, who will review the SDQ scores to establish eligibility. Parents of children who meet age and the SDQ eligibility criteria will be approached by the researcher with an invitation to take part (by email, phone, or post).

#### Method 3: Manual review of current referrals

These methods can be adopted by any organisation participating in the study to either supplement digital identification (via MHE or ICAN) or as a sole way of identifying the eligible families.Consent for contact: members of the clinical teams ask parents of patients if they are happy to be contacted about any relevant research. If they answer yes, this is recorded in their electronic health record and gives Trust-employed Clinical Study Officers (CSOs) or researchers permission to screen their record for suitability and then make direct contact with the parent to invite them to the study.Clinic referral: a member of a clinical team will specifically discuss the study with the parent during a routine clinical contact and if they are interested and give permission then pass their details to CSOs or researchers to take forward from there. This will act as their referral to the study. Information about the study, including a link to access the online information sheet, may also be emailed or posted to families.

### Data collection

Two categories of data will be collected in the feasibility study: (1) participants’ reports on the outcome measures and information about adverse events and (2) the STEPS app usage data (if a participant chooses to use the app).Outcome data and information about adverse events will be collected online using Qualtrics—a secure dedicated survey platform and over the phone by a trained researcher.

#### Online data collection

Researchers will email participants a link to the relevant questionnaires. Participants will need to authenticate (log in) to the online platform using a password before they can view and complete the outcomes survey. After the exit assessment of the final participant is completed, data will be exported and entered into the study database.

#### Phone data collection (pre-baseline)

A trained researcher will ask the feasibility question and administer the three questionnaires during a phone call with a parent. Responses will be logged by a researcher directly into Qualtrics. If requested, parents will be able to complete the three questionnaires online in their own time.(2)All usage data will be collected by Firebase Analytics and will be stored with Google servers. Usage data held within Google Firebase will be generally of non-identifiable nature. Therefore, the risk of harm to participants following a potential privacy breach is low. After data collection has been completed, data will be transferred into the Excel database and Google Firebase account and all the data contained within the account will be deleted.

### Data management

All feasibility, clinical and economic measures will be stored in Qualtrics IBM-SPSS exports and/or a study IBM-SPSS database. The app usage data for the feasibility study will be stored in an Excel database. These databases will be stored on a secure KCL network drive, accessible to the study team only. The study team will provide data extracts to the trial statisticians, upon request.

Data validation will be carried out at the time of data import or entry into the respective SPSS databases to ensure that entered values are valid (e.g., for dates, within an allowed period; for continuous variables, within an allowed range; for categorical, within a list of allowed responses). These validity criteria will be specified in a database specification document, stored in the trial master file.

The study SPSS databases will be stored in a version control system, such that changes made over time can be examined and recovered. All databases will be registered in the King’s Data Protection Register (KDPR).

Any potential data protection breach incidents will be managed in line with KCL Data Breach Management Procedure. For details of this procedure see: https://www.kcl.ac.uk/governancezone/assets/governancelegal/data-breach-procedure.pdf.

De-identified data and identifying information will be stored for seven years from the completion of data collection. After this time, any identifying information will be securely destroyed, and fully anonymised data will be transferred to King’s College Research Data Management system for long-term storage.

### Statistical analysis

This feasibility study will not use inferential statistics to assess the primary objective but will estimate the rate per month of eligible participants who agree in principle to take part in the upcoming STEPS RCT (with the aim of getting 18 per month to give sufficient statistical power to evaluate STEPS in the larger trial planned for later in the programme). Other objectives will be met by using descriptive statistics and qualitative assessments in combination to study the efficiency and acceptability of aspects of the proposed methods. Neither subgroup nor interim analyses are planned in this study. A quantitative statistical analysis plan is being developed.

### Data monitoring

The Programme Steering Committee (PSC), a body independent of the research team, will provide formal oversight and expert advice for the overall OPTIMA programme, which includes oversight over the present feasibility study. Its role is to ensure that the trial is conducted in a rigorous and timely manner and consider any proposed changes to the agreed programme of research. Initially, the PSC will meet every six months with one meeting coinciding with the end of the feasibility study, to determine whether the project should progress to the RCT. The PSC consists of an independent chair, statistician, digital health expert, digital mental health interventions expert, two parents of a child with ADHD, and a health economics expert. Recruitment to the study will be rapid and no interim analyses are planned so a separate Data Monitoring and Ethics Committee (DMEC) will not be formed. However, we reserve the option to form one if the PSC deem it necessary at any point during the study.

